### Sample Size Estimate

Using Stata software version 16.1 IC (StataCorp LLC, College Station, TX), the minimum required number of children to test the intervention was estimated at 20 children aged <5 years per cluster in at least 23 clusters of the control group and 20 in the intervention group. The estimate assumes between-cluster coefficients of variation of 0.38 and 0.19 in the control and intervention groups, respectively (estimated from baseline surveys in clusters assigned to each group), to reach 20 children who were <5 years old per cluster in each group, with assumptions that the proportion of children <5 years old vaccinated in the first month of life will remain at 20.5% (293/1430) based on a survey conducted in the targeted area prior to the intervention [1] and that an α error of .05 and 90% power will detect a 10% increase with the intervention in the proportion of children <5 years old vaccinated with BCG in the first month of their life. The estimate was guided by the method of estimating randomized controlled cluster trials proposed by Batistatou et al [15]. We adjusted to 32 clusters of at least 20 children per study group assuming 10% of the targeted children could not be reached (nonresponse and absence during the survey week) and in order to secure sufficient power to prevent cluster variation of estimated outcomes.

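### On the stated inputs, 23 control and 20 intervention clusters give about 79% power, not 90%; about 31 per arm are needed, so the adopted 32 leaves almost no reserve

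*Protocol article*

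**What the plan says.** All the statements are in the protocol article, Methods, Sample Size Estimate.

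- Minimum size: "20 children aged <5 years per cluster in at least 23 clusters of the control group and 20 in the intervention group".
- Control proportion: it "will remain at 20.5% (293/1430) based on a survey conducted in the targeted area prior to the intervention".
- Error rate, power and effect: "an α error of .05 and 90% power will detect a 10% increase with the intervention". The text does not say whether the test is one- or two-sided, or whether the 10% is absolute or relative.
- Clustering: "between-cluster coefficients of variation of 0.38 and 0.19 in the control and intervention groups, respectively", with the source given as "estimated from baseline surveys in clusters assigned to each group".
- Adopted size: "We adjusted to 32 clusters of at least 20 children per study group assuming 10% of the targeted children could not be reached". The same sentence gives a second reason, which is to protect power against between-cluster variation.

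Under Sampling and Randomization of Clusters, the article describes communities that met one set of eligibility criteria, were stratified, and were allocated in blocks of two within strata.

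**The concern.** The minimum is printed as the result of a calculation whose inputs are all given, so it can be checked, and it does not follow from them. A reader who takes 23 and 20 as sufficient for 90% power will see 32 per arm as a wide safety margin. That margin is the stated protection against cluster variation. If the true requirement is close to 32, the protection is largely absent.

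The margin then depends on the CVs. The intervention arm is planned with half the control arm's CV. Both values describe the arms before any intervention. Randomization from a common pool gives no reason to expect different underlying variation, and the lower value lowers the requirement.

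**Working it through.** **Inputs.** From Sample Size Estimate: p0 = 0.205, m = 20 children per cluster, k0 = 0.38, k1 = 0.19, alpha = 0.05, power = 90%. Assumed: p1 = 0.305 (an absolute rise of 10 points) and a two-sided test. Alternatives are shown below.

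**Formula.** For an unmatched comparison of cluster proportions, the variance of one cluster's proportion in arm i is

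V_i = p_i(1 − p_i)/m + (k_i p_i)²

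and power = Φ(|p1 − p0| / √(V0/c0 + V1/c1) − z_alpha), with c0 and c1 the numbers of clusters.

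- V0 = 0.205 × 0.795/20 + (0.38 × 0.205)² = 0.008149 + 0.006068 = 0.014217
- V1 = 0.305 × 0.695/20 + (0.19 × 0.305)² = 0.010599 + 0.003358 = 0.013957

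**The plan's own figure, 23 and 20 clusters.** SE = √(0.014217/23 + 0.013957/20) = 0.0363. The ratio 0.10/SE is 2.757, so power = Φ(2.757 − 1.960) = 78.7% (76.8% with a t reference). One-sided, Φ(2.757 − 1.645) = 86.7%. The stated 90% is not reproduced.

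**Other readings of the inputs, at 23 and 20 clusters**

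| Reading | Two-sided power |
|---|---|
| CV 0.19 in both arms | 84.9% |
| CVs swapped between arms | 70.0% |
| CV 0.19 applied to p0 rather than p1 | 81.6% |
| Relative 10% rise (20.5% to 22.55%) | about 9% |
| CVs read as cluster-size CVs, ICC 0.005 (assumed; none is stated) | 89.3% |
| The same, ICC 0.02 | 80.8% |
| No clustering at all | 92.0% |

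None of these that allows for clustering reaches 90% two-sided.

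**Clusters needed for 90%, equal arms, two-sided.** (1.960 + 1.282)² = 10.507, so c = 10.507 × (0.014217 + 0.013957)/0.10² = 29.6. That is 30 clusters per arm, or 31 with the customary extra cluster (30.6). One-sided the figure is 26 (25.1 with the extra cluster).

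**The adopted 32 per arm, stated CVs.**

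- 20 children per cluster: SE = √((0.014217 + 0.013957)/32) = 0.0297; power = Φ(3.370 − 1.960) = 92.1% (91.3% by t).
- 18 children per cluster (20 × 0.9): V0 = 0.015123, V1 = 0.015135, SE = 0.0308; power = Φ(3.252 − 1.960) = 90.2% (89.3% by t). The requirement at 18 is 10.507 × 0.030258/0.01 = 31.8 clusters per arm, so 32 is just enough.

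**Sensitivity at 32 per arm with one CV in both arms**

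| Common CV | 20 per cluster | 18 per cluster |
|---|---|---|
| 0.285 (simple mean of 0.38 and 0.19) | 90.7% | 88.7% |
| 0.30 (root mean square) | 89.6% | 87.6% |
| 0.38 | 82.4% | 80.4% |

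With 0.38 in both arms, 90% would take 42 clusters of 20 per arm (41.2).

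**The case against.** The strongest reply is that 23 and 20 is only an intermediate figure. The trial was sized at 32 per arm, and on the protocol's own assumptions that size delivers its 90%. This stands. A reader might infer from the wrong minimum that the trial is underpowered, but the stated inputs do not support that.

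A reader might also infer that the 0.19 has no basis. The text gives one: the baseline surveys, by assigned group. What can be said is narrower: two arm-specific estimates of what should be one quantity are noisy, and planning on the lower one in one arm is favourable. The documents do not show that the gap is due to chance.

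The common CVs of 0.285 and 0.30 are averages formed here and appear nowhere in the article. They also assume that the between-cluster standard deviation grows in proportion as the rate rises to 30.5%. If it instead stayed at 0.30 × 0.205 in both arms, power at 32 per arm would be 93.7% with 20 children and 91.9% with 18. So these figures are sensitivity results and do not replace the stated inputs.

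It is tempting to argue that 10% non-response takes 23 and 20 only to 26 and 23 (23/0.9 and 20/0.9, rounded up), so that 32 is unexplained. That ignores the second reason given in the same sentence, cluster variation.

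Nor can the origin of 23 and 20 be settled. The unclustered size is 10.507 × (0.162975 + 0.211975)/0.01 = 394 children per arm, and 394 × (1 + CV²)/20 gives 22.5 and 20.4, close to both figures. That is not a valid design effect for between-cluster variation, because it leaves out the cluster-size term, and the sizing method cited in the article is not shown. It is a possible explanation only.

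**Conclusion.** The stated minimum is wrong as written. It gives about 79% power two-sided (87% one-sided), and 90% two-sided needs about 30 to 31 clusters per arm. The adopted 32 per arm is adequate on the stated inputs, at 92% with 20 children per cluster and 90% with 18. The margin is one or two clusters per arm, non-response absorbs it, and no real reserve remains for further cluster variation. How robust the 90% is depends on accepting a CV in the intervention arm half that of the control arm. With one CV for both arms, power is about 88% to 91% at 0.285 to 0.30, and 80% to 82% at 0.38.

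These results assume a 10-point absolute effect, a two-sided 5% test, and the standard between-cluster CV variance. The failure of the 23 and 20 minimum does not depend on sidedness.

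**What to change.** In Sample Size Estimate:

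1. Replace the minimum of 23 and 20 clusters with about 31 clusters of 20 children per arm.
2. State the effect as 10 percentage points, from 20.5% to 30.5%, and the test as two-sided at 5%.
3. Report power at the adopted 32 per arm as about 90% to 92% on the stated CVs (18 to 20 children reached per cluster).
4. Add the common-CV results as sensitivity figures: about 88% to 91% at 0.285 to 0.30, and 80% to 82% at 0.38.

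This costs only text. The Results section reports data collection as complete; no clusters are added, and neither design nor analysis changes. The downside is a less favourable stated margin.

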### Data Analysis

The effect of the intervention will be assessed by estimating per study group and comparing (1) yearly immunization timeliness rates for BCG vaccine (proportion of children aged 0-59 months with evidence of vaccination in the first month of life) and measles-rubella vaccine (proportion of children aged 12-23 months with evidence of vaccination while 9-11 months old); (2) coverage of BCG (proportion of children aged 0-59 months who were vaccinated) and DPT-Hi+Hb1, DPT-Hi+Hb3, and measles-rubella (proportion of children aged 12-59 months who were vaccinated) vaccines; and (3) specific completeness (proportion of children who received DPT-Hi+Hb1 and DPT-Hi+Hb3 vaccines) and general completeness (proportion of children who received BCG and measles-rubella vaccines) while aged 12-59 months. Odds ratios for children being vaccinated, being vaccinated on time, and completing vaccination will be estimated and adjusted for the child’s guardians’ level of education and profession, type of population (seminomadic or sedentary), distance to the vaccinating health facility, and religion. The odds ratios will be controlled for variability using logistic regression random effects. The fixed parameters will include the outcome, study groups, child’s guardians’ level of education, type of population (seminomadic or sedentary), child’s guardians’ profession, distance to the vaccinating health facility, and religion, and the random effect will be controlled on the participants’ cluster. The analysis will be done based on the intention to treat principle [16]. Data will be collected using Open Data Kit (ODK)–designed forms on smartphones, verified in the field, and submitted to a secure server. Data will be monitored and cleaned in Microsoft Excel 2013 and analyzed using Stata version 16.1 IC.

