#### Participants

All children aged 0-59 months living in HHs of the selected communities were eligible. This includes the age group targeted by the Cameroon national EPI for routine immunization (0-11 months) and the catch-up vaccination group program (12-59 months) [4]. Children arriving in a HH to stay for less than a month were excluded, and those leaving or planning to stay out of the HH for more than a month were not included. Those leaving the HH for less than a month were not excluded. Parents of children leaving the HH to stay for more than a month were followed up on phone when possible to sensitize them on the necessity of completing the child vaccination program.

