### Outcomes Assessment

Data to assess effects of the interventions were collected from baseline, midline, and endline surveys. The baseline survey also provided data on population characteristics and child access to EPI vaccination prior to the intervention. Each village was mapped using the “my position” function of the Google Earth smartphone app and divided into clusters of about 30 buildings, assuming that each cluster would have at least 20 children aged 0-59 months (based on a pretest conducted in the area). One cluster was randomly selected per village and all its HHs visited for data collection. Data were collected by trained and supervised surveyors from the immunization card, community immunization register, and questionnaire administered to parents of children living in the village. Main data collected included the immunization status and timing regarding BCG, polio zero, DPT-Hi+Hb1, DPT-Hi+Hb2, and DPT-Hi+Hb3 and sociodemographic characteristics. The sampling and implementation process of the surveys were similar but independent [1]. The surveys were conducted by independent survey teams different from the team in charge of implementation of the intervention under investigation.

The primary outcome is the timeliness of documented immunization of children, defined as the proportion of children aged <5 years with documented BCG vaccination status administered within the first month of life.

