### Implementation Procedures

#### Procedures of Survey Implementation

GPS coordinates were collected at the limits of each selected cluster to map and retrieve the map on Google Earth. With the help of community volunteers, the cluster was divided into multiple subclusters of approximately 30 buildings each. One of the subclusters was randomly selected, and all the buildings and inhabited HH of these buildings were visited. All heads of HH were informed by the survey team about the project, and only consenting HHs were enrolled. In these HHs, data were collected from the caregiver for all children aged 0-59 months and from their immunization card about their immunization status as well as any demographic movement in the recent 6 months. The survey lasted for a week in each subcluster. Closed HH that were visited up to 3 times either on the same day or on 3 different days in this period were classified as closed. The study team arranged appointments with the head of HH and children’s guardian(s) if any were busy on the first day of the visit. Heads of HH and guardians who could not be met after 3 appointments on 3 different days were considered as nonrespondents. Children with caregivers refusing to respond to the questionnaire were not included, nor were children normally living in the HH but absent during the data collection period. 

The study questionnaires were pretested and developed into electronic forms by the data management team. Skip patterns and required and formatted fields were used to ensure data accuracy and completeness. Data were collected with smartphones using the ODK Collect application by trained surveyor teams. Each team of 3 surveyors was trained on the study procedures and supervised daily for participant sampling, informed consent, and data collection processes. A protected online server was deployed by the data management team to compile the survey data. During the survey, completed forms were uploaded to the server daily by the supervisor after reviewing and correcting discrepancies. The data management team ensured daily data cleaning, sharing of reports with field supervisors, and monitoring of corrections, updates, and backups. These procedures were the same in both study groups for the baseline, midline, and endline surveys.

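### The BCG timeliness denominator has no minimum age, so infants not yet vaccinated but still inside their first month are scored as not timely

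*Protocol article*

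**What the plan says.** The Outcomes Assessment section defines the primary outcome as the "proportion of children aged <5 years with documented BCG vaccination status administered within the first month of life". The Data Analysis section repeats it as the "proportion of children aged 0-59 months with evidence of vaccination in the first month of life". Neither gives a lower age limit.

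Newborns do enter the survey. Under Participants, "All children aged 0-59 months living in HHs of the selected communities were eligible"; the exclusions there concern short stays and absences, not age. Under Procedures of Survey Implementation, "data were collected from the caregiver for all children aged 0-59 months". Each subcluster is surveyed over one week, and no later check of a newborn's BCG status is described.

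The second timeliness measure in the same Data Analysis sentence, for measles-rubella, is the "proportion of children aged 12-23 months with evidence of vaccination while 9-11 months old". There, every child in the denominator has passed the end of the window.

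**The concern.** Timeliness of a dose due in the first month can be judged in two situations: the dose has been given, or the month is over. For an infant of ten days without BCG, neither holds. The stated rule keeps this child in the denominator and, lacking evidence of vaccination, counts a failure. Some of these infants will be vaccinated in time after the survey team has left.

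This affects the primary outcome, and it is fixed by an age range that the article states, not by a detail left to a fuller document. Each arm's rate is pulled down slightly. Even an equal proportional loss in both arms shrinks the difference between them, so the error runs toward no effect.

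**Working it through.** **Inputs from the article (Sample Size Estimate)**
- Control rate: 293/1430 = 0.2049, which reproduces the stated 20.5%.
- Target: the article says that "an α error of .05 and 90% power will detect a 10% increase with the intervention". I read this as 10 percentage points, so 30.49% in the intervention arm.
- Final size: 32 clusters of 20 children per arm, 32 × 20 = 640 children.
- Variation: "between-cluster coefficients of variation of 0.38 and 0.19 in the control and intervention groups" respectively.

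**Assumptions not in the article**
- Share of surveyed children under one month, f. With even ages over 60 months, f = 1/60 = 1.7%. Range shown: 1% to 3%.
- Fraction of these infants' timely doses still to come on survey day, h. If doses and ages are both spread evenly over the month, h = 1/2. The worst case is h = 1 (none vaccinated yet).
- f and h are the same in both arms.

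**Formula.** Measured rate = true rate × (1 − f × h). The difference shrinks by the same factor.

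| Case | 1 − f × h | Control | Intervention | Difference (points) |
|---|---|---|---|---|
| No open windows | 1 | 20.49% | 30.49% | 10.00 |
| f = 1/60, h = 1/2 | 0.9917 | 20.32% | 30.24% | 9.92 |
| f = 1/60, h = 1 | 0.9833 | 20.15% | 29.98% | 9.83 |
| f = 1%, h = 1 | 0.99 | 20.28% | 30.18% | 9.90 |
| f = 3%, h = 1 | 0.97 | 19.87% | 29.57% | 9.70 |

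**Children affected.** 640/60 = 10.7 infants per arm are under one month. With h = 1/2, those wrongly scored number 10.7 × 0.205 × 0.5 = 1.1 in the control arm and 10.7 × 0.305 × 0.5 = 1.6 in the intervention arm.

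**Odds ratio**, the scale of the planned model: 1.702 with no open windows, 1.697 in the worst case at f = 1/60.

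**Power.** Let V = [p0(1 − p0)/20 + (0.38 p0)² + p1(1 − p1)/20 + (0.19 p1)²]/32, and power = Φ(|p1 − p0|/√V − 1.96), two-sided.
- No open windows: V = (0.01421 + 0.01395)/32 = 0.000880, √V = 0.02967, 0.1/0.02967 − 1.96 = 1.41, power 92.1%.
- Worst case at f = 1/60: V = (0.01391 + 0.01374)/32 = 0.000864, √V = 0.02939, 0.0983/0.02939 − 1.96 = 1.39, power 91.7%.
- Worst case at f = 1% and 3%: 91.9% and 91.4%.

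These power figures use the final 32 clusters per arm. This variance formula does not reproduce the article's minimum of 23 and 20 clusters at 90% power, but that is a separate matter and does not affect the comparison above.

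**The case against.** The strongest objection is size. On the stated 0-59 month denominator, the contrast moves by 0.08 points under the even-spread assumption and by 0.17 in the worst case at 1/60. No conclusion of the trial would turn on that. This stands, and it limits the point to a small correction.

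A second objection is that the phrase about documented BCG status in the outcome definition could confine the denominator to children with a BCG record, so that unvaccinated newborns drop out. The Data Analysis wording does not support that reading: it takes children aged 0-59 months as the base and evidence of vaccination as the numerator.

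A third is that changing a primary outcome after data collection has its own cost. This also stands, and the fix allows for it.

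In the other direction, a reader might infer a larger bias. Infants under one month are 1/12 = 8.3% of children born in a 12-month intervention. In that group 30.5% would read as 30.5 × (1 − 0.083 × 0.5) = 29.2%, a loss of 1.3 points, which would fall on one arm only if control doses were all given near birth. The article does not support this, for two reasons.
- **Denominator.** The stated age range is 0-59 months, and the 10-point target is set for all children under 5. The rates are called yearly, but that word is not defined and does not change the age range. Setting 1.3 points against that target mixes two denominators.
- **Difference by arm.** Nothing in the article shows that intervention doses come later in the first month. Control communities at 5 km or more also have monthly outreach when possible, and nearer ones have weekly facility sessions. In the intervention arm, volunteers promote facility delivery and send newborns to the nearest vaccinating facility when a session is far off, which could make doses earlier. The direction of any difference is unknown.

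**Conclusion.** The point holds as a minor defect of definition. The written rule misclassifies unvaccinated infants whose first month is not over, and the article applies a closed window to its other timeliness measure but not to this one. If 1/60 of the children are under one month and the loss is proportional in both arms, a true 10-point difference reads as 9.92 points, or 9.83 at worst. A share of 1% to 3% gives 9.9 to 9.7 in the worst case. Power falls by less than one percentage point. The result is a slight dilution toward no effect; it does not create a false effect, and a loss concentrated in one arm is not shown. The share under one month is an assumption that the survey data can replace directly.

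**What to change.** Compute the primary outcome and the BCG timeliness rate among children who have completed one month of age on survey day, for example: children aged 1-59 months at the survey with documented BCG given in the first month of life. Use the same length of month for the age limit and for the vaccination window. Leave the BCG coverage denominator at 0-59 months, since coverage on survey day is observable at any age.

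The Results section says that data collection was completed by January 2020. The change should therefore be recorded, with its date, as made before the arms were compared, and the 0-59 month version reported as a sensitivity analysis. If the arms have already been compared, the stated version should stay primary, with the 1-59 month version beside it.

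Cost: no new data are needed. About 1 in 60 children leave the primary denominator. The definition also departs slightly from the planning rate, which is described for all children under 5 and which the article assumes "will remain at 20.5% (293/1430) based on a survey conducted in the targeted area prior to the intervention". If that figure carries the same feature, the rate on the new denominator would be at most 20.49/(59/60) = 20.84%, about 0.35 points higher at f = 1/60.

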### Sampling

#### Sampling and Randomization of Clusters

To be eligible, communities had to have limited access to a vaccinating health facility and either have recorded a case of EPI-PD in the previous 12 months or belong to a health area with administrative DPT-Hi+Hb3 vaccine coverage <70% in the routinely EPI-targeted population. Communities with limited seasonal accessibility limiting the monitoring of the intervention in some period of the implementation of the intervention were excluded.

In this study, we considered a “community” to be the smallest geographic area (quarter) with a traditional leader (commonly called head of quarter) gathering 100-300 HHs in rural areas or 200-500 HHs in urban areas.

Selected communities were stratified according to their setting (urban/rural), the importance of yearly population movement, the distance to the vaccinating health facility, and the occurrence of EPI-PD in the previous year. In each stratum, communities were ranked in alphabetic order from A to Z and in blocks of 2. All combinations of blocks were listed, and a 1-digit number was assigned to each combination. Numbers were generated from Table XXXIII of Wishart [14], as follows: An arbitrary point was chosen in the table, and numbers were read in a single digit row by row across the page. Each number read and corresponding to a pair of communities dictated the distribution of these communities by study group. Randomized communities were divided into subunits of up to 200 buildings (ranging 100-150 HHs) called clusters using the Google Maps app installed on a smartphone. From previous experience, this is the number of buildings that can be visited in a week by a community volunteer to implement planned activities. One of these clusters per village was randomly chosen per village in each study group. To be able to compare immunization coverage and other indicators between baseline, midline, and endline surveys, eligible but not selected communities were similarly and independently randomized but did not receive the intervention.

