Secondary outcomes include the documented completeness of general EPI vaccination of children, defined as the proportion of children who started vaccination with BCG and who completed it by receiving the measles-rubella vaccine, as documented on the immunization card, and documented completeness of specific immunization of children, defined as the proportion of children who received DPT-Hi+Hb1 and who completed pentavalent vaccination doses by receiving the DPT-Hi+Hb3 vaccine, as documented on the immunization card. In addition, we will assess the timeliness of overall immunization of children, defined as the proportion of children completing all their EPI-recommended vaccines within the first year of life, as documented on the immunization card or not documented but tracked from caregiver memory, and completeness of overall immunization of children, defined as the proportion of children who started vaccination with BCG and completed it by receiving the measles-rubella vaccine, as documented on the immunization card or not documented but tracked from caregiver memory. Documented coverage of child immunization is defined as the proportion of children who will have received DPT-Hi+Hb3, as documented on the immunization card, and overall coverage of child immunization is defined as the proportion of children who have received DPT-Hi+Hb3, as documented on the immunization card or tracked from caregiver memory. We will also assess the documented recruitment rate, defined as the proportion of children starting vaccination with BCG, as documented on the immunization card, and the overall recruitment rate, defined as the proportion of children starting vaccination with BCG, as documented on the immunization card or tracked from their mother’s memory.

The effects of the intervention will be assessed by comparing completeness, timeliness, and coverage estimated from the intervention and control groups.

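### The stated effect model has no term for the cluster's baseline timely-BCG level or for survey round, so it gives up some available precision and leaves the analysed round open

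*Protocol article*

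**What the plan says.** All references are to the protocol article.

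- **Data Analysis** gives the odds-ratio model term by term: "The fixed parameters will include the outcome, study groups", guardian education, population type, guardian profession, distance to the vaccinating facility and religion. For the random part, "the random effect will be controlled on the participants", and the sentence goes on to name the cluster. No baseline level, survey round or group-by-round term appears.
- **Outcomes Assessment** says: "Data to assess effects of the interventions were collected from baseline, midline, and endline surveys". It defines the contrast without naming a round: "The effects of the intervention will be assessed by comparing completeness, timeliness, and coverage estimated from the intervention and control groups".
- **Sample Size Estimate** shows that baseline results were available by cluster and arm, since the design CVs of 0.38 and 0.19 were "estimated from baseline surveys in clusters assigned to each group".
- The surveys are repeated cross-sections: "The sampling and implementation process of the surveys were similar but independent". Within a cluster, "One of the subclusters was randomly selected, and all the buildings" in it were visited (Procedures of Survey Implementation).
- Randomisation was restricted: "Selected communities were stratified according to their setting (urban/rural), the importance of yearly population movement, the distance to the vaccinating health facility" and previous outbreak status, in blocks of 2.

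**The concern.** The term list does not match the data the article says it will use. Three surveys feed the effect assessment, but the model cannot tell one survey from another. Two readings are open.

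- **Endline only.** The most obvious prognostic covariate, the cluster's own baseline level of the primary outcome, goes unused even though it has been measured.
- **Rounds pooled.** The single group coefficient mixes baseline children, on whom the intervention cannot have acted, with later children, and the effect is diluted.

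Data collection is complete and analysis is under way (Results), so which round gives the primary estimate should not be left to choice after the data are seen.

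**Working it through.** **Inputs.** From Sample Size Estimate: control proportion p0 = 0.205, CVs k0 = 0.38 (control) and k1 = 0.19 (intervention), m = 20 children per cluster, 32 clusters per arm. My assumptions: the 10% increase means 10 points (p1 = 0.305); alpha 0.05 is two-sided; the CVs describe variation in the outcome proportion; the true baseline and endline cluster levels correlate at c = 0.7 to 0.9. The article gives no value for c.

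**1. The plan's own size.** The variance of a cluster mean is p(1−p)/m + (kp)².
- Control at endline: 0.00815 + 0.00607 = 0.01422.
- Intervention at endline: 0.01060 + 0.00336 = 0.01396.
- Sum 0.02817; divided by 32 and square-rooted, SE = 0.0297.
- Power = Φ(0.10/0.0297 − 1.96) = 92.1%.

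The stated minimum of 23 and 20 clusters gives 78.7% two-sided (86.7% one-sided) by the same formula, so 90% is not reproduced there. That is a separate matter. The comparison below uses 32 per arm.

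**2. Chance baseline imbalance.**
- Baseline cluster-mean variances: control 0.01422; intervention 0.00815 + 0.00152 = 0.00967; sum 0.02388.
- Observed difference: SD = √(0.02388/32) = 2.7 points.
- Between-cluster part only: 0.00607 + 0.00152 = 0.00759; SD = √(0.00759/32) = 1.5 points, 95% range about ±3.0 points. With one CV in both arms the range is ±1.9 (0.19) to ±3.8 (0.38).
- Share of the observed variance that is true cluster variation: 0.00759/0.02388 = 32%. The other 68% is sampling of about 20 children per cluster.
- A true 3-point difference persisting to endline (19.0% against 22.0%) gives OR = (0.22/0.78)/(0.19/0.81) = 1.20 with no effect.

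**3. Endline model with the cluster baseline proportion.**
- Baseline-endline covariance: control c × 0.00607; intervention c × (0.19 × 0.205)(0.19 × 0.305) = c × 0.00226; sum c × 0.00833.
- With one common slope, the proportional variance cut is (c × 0.00833)²/(0.02388 × 0.02817) = 0.103c².
- c = 0.7: cut 5.0%, power 93.3%. c = 0.9: cut 8.3%, power 94.1%.
- Sensitivity, same CV and rate in both arms: the cut is (reliability × c)². With CV 0.19 and c = 0.5 it is (0.157 × 0.5)², about 1%. With CV 0.38 and c = 1 it is 0.427², about 18%.

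**4. Unconstrained group-by-round contrast (endline change minus baseline).**
- Variance sum: 0.02817 + 0.02388 − 2c × 0.00833.
- c = 0.7: 0.0404, which is 1.43 times the endline-only 0.02817; power about 80%.
- c = 0.9: 0.0371, which is 1.32 times; power about 84%.

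**5. Pooling without a round term.**
- One third baseline data, full effect in the rest: 10 × 2/3 = 6.7 points (27.2% against 20.5%); OR 1.45 instead of 1.70.
- One half baseline data: 5.0 points, OR 1.33.
- Three equal rounds with midline at half the endline effect, which is an assumption: 10 × (0 + 0.5 + 1)/3 = 5.0 points.

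**The case against.** **The article condenses a fuller plan, and the primary round may be named there.** This is fair as to the round. It is weaker as to the covariates, because the article states the list of terms in full and the baseline level is not on it.

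**Pooling is written nowhere.** This stands. The article speaks of yearly rates per study group and of comparing indicators between surveys, and it gives the baseline survey a descriptive purpose as well. These point towards round-specific estimates. A reader might infer from the three-survey sentence that one pooled regression is planned, and that the effect will be halved. The documents do not say so, and the dilution figures are conditional on that reading.

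**Leaving out the baseline does not bias the result.** This also stands. A reader might infer that chance imbalance passes straight into the conclusion. Randomisation keeps the contrast unbiased, and the random cluster effect carries between-cluster variation into the standard error. Stratification in blocks of 2, with distance and population type in the model, narrows the imbalance further.

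**The imbalance looks larger than it is.** The observed difference has a 95% range of 1.96 × 2.7, about ±5.4 points, over half the target. That should not be read as imbalance carried forward to endline. About 68% of its variance is sampling noise, and because the samples are drawn independently most of that is not expected to recur. One point cuts the other way. The outcome covers ages 0-59 months and the intervention ran 12 months, so with evenly spread ages (an assumption) about 48/60 = 80% of endline children had their first-month BCG status settled before it began. That favours a high persistence of true cluster levels, but it does not make the sampling noise persist.

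**The precision gain is small.** Agreed: one to two points of power on the stated inputs. Omitting the covariate is a defensible choice, though one that gains nothing when the data are already in hand.

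**Conclusion.** The point holds as a modest, low-cost improvement and a needed clarification. It is not a threat to validity. The stated model uses neither the cluster baseline level nor the survey round. The cost is a variance reduction of about 5-8% forgone (power about 92% instead of 93-94% at 32 clusters per arm), a true chance difference of up to about ±3.0 points left unadjusted before credit for stratification, and an open question about which survey gives the primary estimate. Pooling rounds without a round term would cost far more, but the article does not commit to it. These figures rest on the stated CVs applying to the outcome proportion, a 10-point effect, a two-sided test and an assumed cluster correlation of 0.7 to 0.9.

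A group-by-round interaction is not an equivalent remedy. With only about 20 children per cluster the baseline means are too noisy, and differencing them would take power below the 90% target.

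**What to change.** In the analysis plan:

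1. Name endline as the round for the primary contrast and make midline secondary.
2. Fit the primary model to endline children with the terms already listed, plus the cluster's baseline proportion of timely BCG as a fixed covariate. It has to be a village-level value, because different children and possibly different subclusters are surveyed each time. Confirm that each endline village has a baseline value.
3. If all rounds are to be modelled together, include round, cluster and cluster-by-round random effects, and constrain the baseline group difference to zero. Do not take an unconstrained group-by-round contrast as the primary effect.

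The cost is one covariate from data already collected and a few lines of wording. Since collection is complete, the choice should be fixed and dated before the arms are compared.
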